#### Cost and Health Economic Outcomes

These will include total costs at 12 months and Quality-adjusted Life Years (QALYs) at 12 months. Total costs will be calculated by valuing the resource use for delivering the interventions, length of stay in PICU and hospital, and wider NHS resource use up to 12 months.

QALYs at 12 months will be calculated from HrQoL and survival data. Incremental net monetary benefit (INB) at 12 months associated with permissive MAP target vs. usual care will be derived from incremental costs and QALYs at 12 months. INB will be calculated by valuing QALY gains at the National Institute for Health and Care Excellence (NICE) recommended (£20,000) willingness to pay for a QALY gain and subtracting incremental costs.

### Clinical Effectiveness Analysis Methods

#### Primary Outcome

The primary clinical outcome will be summarized by arm (median, IQR, graphically) and analyzed using a two-sample rank-sum (Wilcoxon-Mann-Whitney) test (10). The primary effect estimate will be the probabilistic index, the probability that intervention is superior to control for the composite outcome, and 95% CI. The separate components will also be presented by arm with effect sizes and 95% CIs, following established guidelines (11). Mortality will be analyzed using logistic regression, adjusting for age (younger than1 yr; 1 yr to younger than 3 yr; 3 yr or older), and site as a random effect. Duration of IMV will be analyzed using a two-sample rank-sum test.

Ordered logistic regression will estimate the proportional odds ratio, adjusting for baseline variables. The unadjusted OR will be presented for comparison. If data completeness allows, the following variables will be used in adjusted analyses: predicted log odds of mortality at randomization (Paediatric Index of Mortality, version 3 [PIM-3] score (12) [continuous; linear]); primary reason for admission (suspected/proven infection vs. other); comorbidities (neurologic vs. non-neurologic vs. none); age (continuous; restricted cubic splines with four knots at the 5th, 35th, 65th, and 95th percentiles); and site (random effect).

Baseline covariates were prespecified based on anticipated associations with the outcomes. Results will be reported as adjusted odds ratios with 95% CI.

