**SETTING::**

Twenty-one PICUs in the United Kingdom.

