## METHODS

### Trial Design and Randomization

PRESSURE is a pragmatic, multicenter, parallel group, superiority randomized controlled trial. Eligible patients are randomized to either usual care or the permissive MAP target arm (age-dependent target). Allocation is by randomized permuted blocks with variable block lengths, stratified by site and age category (younger than 12 mo; 1 yr to younger than 3 yr; 3 yr or older).

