The CEA will follow ITT principle and will use appropriate regression methods. The interclass correlation coefficient (ICC) will be calculated which measures the proportion of the overall variation at the cluster level. If ICC greater than 10%, multilevel models (MLMs) will be used to handle clustering and avoid potential biases and incorrect inferences. The CEA model will adjust for key baseline covariates as per the primary clinical analysis. Missing data in health economic endpoints will be handled with appropriate multiple imputation methods, assuming the data are missing at random conditional on the observed data (20). On the imputed datasets the CEA will use a Bivariate Seemingly Unrelated Regression model to allow for correlation between costs and QALYs (21). The incremental results from multiply-imputed datasets will be summarized using Rubin’s rule (22).

The CEA will report the mean (95% CI) incremental costs, QALYs and net monetary benefit at 12 months. Results uncertainty will be summarized and represented on a cost-effectiveness plane and using acceptability curves. The CEA will report results for the overall patient group and subgroups as per the primary clinical analysis.

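### The primary rank-sum test, its probabilistic index and the interim test ignore the site and age strata used to randomise, so they are mildly conservative to the extent that site and age predict outcome

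*SAP article*

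**What the plan says.** Under Trial Design and Randomization, allocation uses permuted blocks of varying length, "stratified by site and age category (younger than 12 mo; 1 yr to younger than 3 yr; 3 yr or older". The Abstract gives the setting as "Twenty-one PICUs in the United Kingdom", so there are up to 21 × 3 = 63 strata.

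Under Clinical Effectiveness Analysis Methods, Primary Outcome, the composite is "analyzed using a two-sample rank-sum (Wilcoxon-Mann-Whitney) test (10". The estimate to go with it is set out as follows: "The primary effect estimate will be the probabilistic index, the probability that intervention is superior to control for the composite outcome, and 95% CI". Neither sentence mentions site or age. The IMV component is treated in the same way: "Duration of IMV will be analyzed using a two-sample rank-sum test". The section on interim analyses names the same two-sample test, with stopping at p < 0.001.

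The other component is handled differently: "Mortality will be analyzed using logistic regression, adjusting for age" in the three randomisation bands, with site as a random effect. There is also a supporting model for the composite: "Ordered logistic regression will estimate the proportional odds ratio, adjusting for baseline variables". Its covariates include age and site, and the section says the covariates were chosen because they were expected to relate to the outcomes. The article gives no reason for leaving the strata out of the primary test.

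**The concern.** Blocking within strata holds the arms close to balanced on site and age. Differences between strata then contribute almost nothing to the true sampling variation of the treatment comparison. A plain rank-sum test still counts those differences in its variance. If the strata are prognostic, the p-value is therefore somewhat too large and the interval somewhat too wide.

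The plan appears to expect them to be prognostic, since it lists age and site among its chosen adjusters and adjusts mortality for exactly these two factors. At stake is a little precision and power in the one analysis that decides superiority, and in the one that governs early stopping.

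**Working it through.** **Inputs from the SAP article.** Two-sided alpha 0.05 (CIs and p Values). From Sample Size: 1900 randomised, 10% lost, so 1900 × 0.90 = 1710 analysed, or 855 per arm if allocation is equal; mortality 13% vs 11%; log-normal IMV duration with mean 7.8 d and SD 9.5 d; an 18-hour (0.75 d) reduction, giving 7.05 d (printed as 7.1 d); power 90%. Deaths score 31 (Primary Clinical Outcome).

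**Assumed, not in the article.** R², the share of rank variance explained by site and age; equal allocation; block sizes 4 and 6; site sizes and age mix; an interval built from the usual unstratified variance.

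**1. The plan's own figure.** In 2,000 simulated trials with the inputs above, and SD 9.5 d in both arms, the unstratified test has power 90.2% (whole days) to 91.2% (continuous). With the printed 7.1 d it is 88.3% to 88.5%. So the stated 90% reproduces for the test the plan names. This depends on the SD being held at 9.5 d. Scaling the SD with the mean gives 62% to 66%, so the design appears to have held it fixed.

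**2. Analytic effect of ignoring the strata.** Under stratified blocks the true variance is about (1 − R²) times the variance the test assumes. Then:

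- true alpha = 2 × [1 − Φ(1.96/√(1 − R²))]
- excess CI width = 1/√(1 − R²) − 1
- power, planned test = Φ(1.2816/√(1 − R²))
- power, strata-adjusted = Φ(3.2415/√(1 − R²) − 1.96)

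Here 3.2415 = 1.96 + 1.2816, the shift that gives 90% power when R² = 0. For R² = 0.10, √0.90 = 0.9487 and 1.96/0.9487 = 2.066, so alpha is 3.9%. The excess width is 1/0.9487 − 1 = 5.4%.

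| R² | True alpha | CI too wide by | Power, planned | Power, adjusted |
|---|---|---|---|---|
| 0 | 5.0% | 0% | 90.0% | 90.0% |
| 3% | 4.7% | 1.5% | 90.3% | 90.8% |
| 5% | 4.4% | 2.6% | 90.6% | 91.4% |
| 10% | 3.9% | 5.4% | 91.2% | 92.7% |
| 16.5% | 3.2% | 9.4% | 92.0% | 94.4% |

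**3. Simulation check.** 2,000 trials per scenario, 1710 children, 21 sites × 3 age bands. The planned test was compared with a rank regression on arm, site and age band, and with the van Elteren test over 63 strata. The Monte Carlo SE is about 0.5 points for alpha and 0.6 points for power.

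| R² (about) | Alpha: planned / rank regression | Power: planned / rank regression / van Elteren |
|---|---|---|
| 0 | 5.8% / 5.6% | 90.1% / 90.2% / 89.4% |
| 3% | 4.0% / 4.4% | 91.7% / 92.1% / 91.7% |
| 9% | 3.9% / 5.1% | 91.6% / 93.1% / 92.0% |
| 16.5% | 2.9% / 4.6% | 91.4% / 93.8% / 93.8% |

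The simulation agrees with the formulas in direction and roughly in size. The planned test falls below 5% as R² grows, while the adjusted test stays near 5%. Power forgone is about 0.5 to 2.5 points over R² of 3% to 16.5%, and essentially nil at zero.

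**4. Stratum size.** 1710/63 is about 27 children per stratum at the end and 950/63 about 15 at interim. These are averages; site sizes are not given, and some strata will be sparse.

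**The case against.** The strongest reply is that nothing stated is invalid. The test does not inflate type I error, and it delivers the 90% power claimed for it; the loss is only relative to a test on which the design never relied. A mildly conservative interim test at p < 0.001 adds no risk of stopping falsely. All of this stands.

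The reply also says that the size rests on an assumed R². The sentence about expected associations covers the whole adjuster list and puts no number on site and age. This stands too, and it is why a range is given.

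A third argument is that the adjusted ordinal model already uses age and site, along with PIM-3, reason for admission and comorbidity. It does, but it yields an odds ratio. It supplies neither the primary p-value, nor the probabilistic index, nor the interim decision, so it offsets the point only in part.

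Finally, a 63-stratum van Elteren test is not clearly the best remedy. The simulation bears this out: rank regression was slightly better at about 3% and 9%, and level at 16.5%. A within-stratum index is also a different quantity from the overall one.

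A reader might further infer that the economic section points to an empty reference when it says "The CEA model will adjust for key baseline covariates as per the primary clinical analysis", because the primary test has no covariates. The document does not support that reading: the Primary Outcome section lists baseline covariates for a model of the primary outcome, and these are a natural referent.

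**Conclusion.** The point holds as a modest improvement in efficiency and calibration. The primary test, its index and CI, the interim test and the IMV component leave out strata that the design balances and that the same section uses for mortality.

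If site and age explain 3% to 10% of rank variance, true alpha is about 4.7% to 3.9% and the CI about 1.5% to 5.4% too wide. Over 3% to 16.5%, about 0.5 to 2.5 points of power are forgone. The direction follows from the design, but the size depends on an R² that the document does not give, and the effect vanishes if the strata are not prognostic.

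A reader might infer that the trial is underpowered or its test invalid. Neither follows: the error is on the conservative side, and the stated power is met when the SD is held at 9.5 d.

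**What to change.** Make a strata-respecting rank analysis primary. One option is a rank-based or probabilistic index model adjusted for age band and site. The other is a van Elteren test with a prespecified rule for pooling sparse sites. Report the matching probabilistic index with 95% CI, and state whether it is the overall or the within-stratum index. Use the same analysis at interim and for IMV duration, and keep the unstratified rank-sum test as a sensitivity analysis. The change should be fixed before anyone sees outcomes by arm.

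The cost is SAP wording and a little code; no new data are needed. The index changes slightly in meaning if it is made conditional on strata. If the strata turn out not to be prognostic, the power cost is negligible: in the simulation 90.2% with covariate adjustment and 89.4% with 63-stratum van Elteren, against 90.1% as planned, which are differences of about one Monte Carlo SE or less.

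### The primary probabilistic index is left unadjusted although the SAP names PIM-3 and other covariates it expects to be prognostic: a missed efficiency, not an error

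*SAP article*

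**What the plan says.** All of this is in the SAP article. Under Clinical Effectiveness Analysis Methods, Primary Outcome:

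- The composite is "analyzed using a two-sample rank-sum (Wilcoxon-Mann-Whitney) test".
- The estimate is fixed as follows: "The primary effect estimate will be the probabilistic index, the probability that intervention is superior to control for the composite outcome". No covariate enters either.
- The components differ in treatment. For death: "Mortality will be analyzed using logistic regression, adjusting for age (younger than1 yr; 1 yr to younger than 3 yr; 3 yr or older), and" (a random effect for site follows). For ventilation: "Duration of IMV will be analyzed using a two-sample rank-sum test".
- A supporting ordered logistic model is adjusted, subject to data completeness, for the "predicted log odds of mortality at randomization (Paediatric Index of Mortality, version 3 [PIM-3] score (12) [continuous; linear"], reason for admission (infection or other), comorbidity, an age spline and site. The plan adds: "Baseline covariates were prespecified based on anticipated associations with the outcomes".

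Elsewhere, Table 3 lists 30-day mortality again as a secondary outcome. The analysis section for secondary outcomes gives it a Fisher exact test, plus a baseline-adjusted logistic regression where judged suitable. The interim analysis uses the same unadjusted rank-sum test.

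**The concern.** The composite gives death the worst score, so a baseline predictor of death should explain part of the variation in its ranks. The plan itself expects these covariates to be associated with the outcomes. An unadjusted comparison leaves that explainable variation in the standard error of the primary index, although the adjustment set is already chosen. At stake is some power for the main conclusion, obtainable without recruiting more children.

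A smaller issue sits beside it. 30-day mortality is analysed in two places with different covariates, and only one of them could include PIM-3.

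**Working it through.** **Inputs from the SAP article.** Sample Size: 1900 children, 10% withdrawal, mortality 13% v 11%, log-normal ventilation with mean 7.8 d and SD 9.5 d, an 18-hour reduction in survivors (printed as 7.8 to 7.1 d), 90% power. Primary Clinical Outcome: death = 31, survivors scored in calendar days to day 30. CIs and p Values: two-sided 0.05. Assumed, because not stated: 1:1 allocation, the intervention-arm SD, and the prognostic strength of PIM-3.

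**Step 1: the plan's own power.** Analysed: 1900 × 0.90 = 1710, or 855 per arm. Control log-normal: σ² = ln(1 + (9.5/7.8)²) = 0.910, μ = ln 7.8 − 0.910/2 = 1.599. Intervention with 18 h = 0.75 d, so mean 7.05 d and SD 9.5 d: σ² = ln(1 + (9.5/7.05)²) = 1.035, μ = ln 7.05 − 1.035/2 = 1.435. Unadjusted rank-sum power:

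| Intervention mean, SD | Power | Simulated trials |
|---|---|---|
| 7.05 d, SD 9.5 | 90.8% (whole days), 91.4% (continuous) | 10,000 |
| 7.1 d, SD 9.5 | 87.7% and 88.2% | 10,000 |
| 7.1 d, SD 9.5 (separate run) | 86-87% | 3,000 |
| constant coefficient of variation | about 60-68% | 2,000 |

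The stated 90% therefore reproduces for the unadjusted test with the 18-hour effect and equal SDs.

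**Step 2: standard error of the index.** A PIM-3-like normal covariate was added and the index estimated by rank analysis of covariance (1,000 trials per row). The expected ratio of standard errors is √(1 − R²), where R² is the share of composite-rank variance explained.

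| AUC for death / correlation with log IMV (both assumed) | R² | SE unadjusted → adjusted | Cut | √(1 − R²) |
|---|---|---|---|---|
| 0.64 / 0.1 | 2.7% | 0.01387 → 0.01369 | 1% | 0.986 |
| 0.71 / 0.2 | 7.8% | 0.01387 → 0.01332 | 4% | 0.960 |
| 0.75 / 0.3 | 13.8% | 0.01387 → 0.01287 | 7% | 0.928 |
| 0.80 / 0.4 | 21.9% | 0.01387 → 0.01225 | 12% | 0.884 |

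**Step 3: power.** Power = Φ((z + 1.96)/√(1 − R²) − 1.96), where z is the normal quantile of the unadjusted power. From 90%, z + 1.96 = 1.2816 + 1.96 = 3.2416. For R² = 22%: 3.2416/0.8832 − 1.96 = 1.710, giving 95.6%.

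| R² | From 90% | From 91% |
|---|---|---|
| 3% | 90.9% (+0.9) | 91.8% (+0.8) |
| 8% | 92.2% (+2.2) | 93.1% (+2.1) |
| 14% | 93.8% (+3.8) | 94.5% (+3.5) |
| 22% | 95.6% (+5.6) | 96.2% (+5.2) |

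The simulated pairs (rank-sum → rank ANCOVA) were 90.8 → 90.8, 91.2 → 93.4, 92.1 → 95.1 and 89.0 → 95.2%. Each power carries a Monte Carlo error of about √(0.9 × 0.1/1000) = 0.9 points, so they agree with the formula. With no prognostic value the pair was 91.2 → 91.1%. Under the null (AUC 0.75 case) both tests rejected in 5.7% of trials.

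**Step 4: odds-ratio scale.** In the strongest case the ordinal log-OR standard error goes from 0.084 to 0.085 while the log OR moves from −0.27 to −0.31. For death alone the standard error goes from 0.150 to 0.164 and the log OR from −0.19 to −0.23. The gain there is in power, not in a narrower interval. Mortality power in the individual runs (3,000 trials each) was 23.9 → 24.0, 23.3 → 26.8 and 24.6 → 29.5% at AUC 0.64, 0.75 and 0.80. On the standardised risk difference, a separate simulation at assumed AUC 0.68 / 0.75 / 0.80 found variance about 5 / 12 / 18% lower.

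**The case against.** The strongest reply is that nothing is broken. The rank-sum test is valid, the trial was sized for it, the interim uses it, and it keeps every child with outcome data without imputing covariates. That stands, and it is why this is an efficiency point only.

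Three stronger readings are tempting, and the documents do not support them:

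- A reader might infer that PIM-3 is used only in the ordered logistic model. The secondary-outcomes section foresees baseline-adjusted logistic regression for mortality, including at 30 days, though only conditionally.
- A reader might infer that the primary result is less precise than a model the SAP already contains. That model estimates a conditional odds ratio, whose standard error does not shrink with adjustment. Precision improves on the probabilistic-index scale, with an adjusted index that the SAP does not specify.
- A reader might assume a correlation of 0.5 between PIM-3 and the composite rank, giving 96.3% power. That is R² = 25%, above the strongest case worked here, and the documents give no figure.

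The missing-data objection also has force. Under Consent, linkage stops if records access is declined, yet primary outcome data are still collected. Under Baseline Patient Characteristics, admission data come by linkage to the national audit. If PIM-3 comes by that route, some children will have an outcome but no PIM-3. Consent follows randomisation in an open trial, so availability could depend on arm. This rules out a missing-category indicator, but it does not defeat adjustment. Finally, the absence of a stated rationale carries no weight in a condensed article.

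**Conclusion.** The point holds as a missed efficiency, not as an error or a shortfall against the design. For assumed R² of 3-22%, adjusting the primary index cuts its standard error by about 1-12% and adds roughly 0.5 to 5 power points. The closed form gives 0.8 to 5.2 from the reproduced 91%, and up to 5.6 from 90%. If PIM-3 is weak the gain is near zero, and so is the loss.

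These figures rest on one covariate, 855 per arm, equal SDs and an assumed prognostic strength. The contribution of infection and comorbidity was not quantified.

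For 30-day mortality the gain is small, about 1 to 4 points from about 25% (nearly 5 in the strongest single run). A narrower interval arises only on a marginal scale such as the standardised risk difference. The stronger reason to act there is that two sections analyse the same outcome differently.

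**What to change.** Before unblinding:

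1. Keep the probabilistic index as the primary estimand, but estimate and test it with the covariates already listed under Primary Outcome, for example by rank analysis of covariance or a covariate-adjusted Mann-Whitney estimator. Neither needs proportional odds. Report the plain rank-sum test and unadjusted index beside it.
2. Align the interim analysis wording, or state that the interim stays unadjusted.
3. Use only covariate values fixed before randomisation. Fill missing values with an overall mean or mode computed blind to arm, not with a missing-category indicator, so that every child in the primary analysis population stays in.
4. For 30-day mortality, use one model with the listed covariate set including PIM-3, and name it in both the component analysis (now age band and site) and the secondary-outcome analysis (now Fisher exact, with adjusted regression where suitable). If a narrower interval is wanted, report the standardised risk difference with the odds ratio.

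The cost is SAP wording and a few lines of code, with no new data or patients. The downside is a slightly less simple primary analysis that depends on PIM-3 completeness.

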#### Secondary Outcomes

Mortality outcomes will be compared using Fisher exact test. If suitable, logistic regression will be used, adjusted for baseline variables.

Duration of survival will be plotted as Kaplan-Meier survival curves by arm. An adjusted hazard ratio will be calculated using Cox proportional hazards regression.

Time to liberation from IMV will be reported as median time (with 95% CI) by arm using Kaplan-Meier methods. An adjusted hazard ratio will be calculated using Cox proportional hazards regression.

Change in functional status will be analyzed using adjusted linear regression, additionally adjusting for baseline status. Receipt of RRT at 30 days will be reported as median and IQR for patients surviving to day 30 and compared between groups using a Wilcoxon rank-sum test. Length of PICU and acute hospital stay will be compared using a Wilcoxon rank-sum test and reported by group using medians and IQRs in patients stratified by survival status. HrQoL score for survivors (12 mo) will be reported and a linear regression model adjusting for baseline variables will be applied to report incremental effect.

#### Subgroup Analyses

If sample sizes allow and following established guidelines (13, 14), subgroup analyses will test for interactions between treatment allocation and baseline covariates: age (continuous); infection (proven/suspected; none); comorbidities (neurologic vs. non-neurologic vs. none); PIM-3 score (continuous).

Where data completeness is below an acceptable threshold, multiple imputation may be used, or the relevant subgroup removed. The Instrument to Assess the Credibility of Effect Modification Analyses tool will assess the credibility of subgroup findings (15).

#### Sensitivity Analyses

The primary analysis will be repeated adjusting for adherence to allocated intervention (as a binary variable indicating any “unacceptable” deviation and/or as a continuous variable with percentage of treatment hours with no “unacceptable” deviation) using a structural mean model with an instrumental variable of allocated treatment to estimate the complier average causal effect of treatment (16). If convergence cannot be achieved, a per protocol analysis will be performed.

